## Abstract

**Background:**

Temporomandibular disorders (TMD) is a disease characterized by pain and dysfunction of the masticatory muscles and temporomandibular joint. Many factors have been found to be related to the disease however, the underlying mechanism is yet to be fully elucidated. Physical activity is widely known to modulate pain intensity in various pain disorders. However, literature suggesting the association between physical activity and signs and symptoms of TMD are limited.

**Methods and design:**

The “Physical Activity in TMD (PAT)” is a prospective study on TMD patients that aims to determine how daily physical activity and sleep duration affect long-term TMD prognosis following conventional treatment. To analyze such effects, objective data on daily physical activity levels will be collected along with clinical indices including mouth opening ranges and masticatory muscle palpation responses from adult Koreans diagnosed with TMD following standardized diagnostic procedures. Well-known comorbidities of TMD will be extensively evaluated based on validated structured questionnaires on sleep quality, fatigue level, widespread pain, psychological status including depression and anxiety, autonomic symptoms, and health-related quality of life. The collected data will be analyzed according to TMD pain severity and physical activity level, and correlations among physical activity indices and long-term TMD prognosis will be investigated.

**Discussion:**

In this longitudinal prospective study of adult Koreans diagnosed with TMD following standardized diagnostic procedures, primary outcomes include physical activity levels and long-term TMD clinical outcomes and secondary outcomes include disability from pain and related comorbidity levels. Results and analysis are ongoing. The results of this study will provide reliable data for future research and establish clinical guidelines that will allow cause-related, patient-tailored personalized medicine for TMD.

*Trial registration*: Clinical Research Information Service (Registration number: KCT0007107). Registered March 22 2022 https://cris.nih.go.kr/cris/search/detailSearch.do?search_lang=E&focus=reset_12&search_page=M&pageSize=10&page=undefined&seq=21420&status=5&seq_group=21420.

## Background

Temporomandibular disorders (TMD) is a disease usually represented by discomfort and/or dysfunction of the masticatory muscles and temporomandibular joints (TMJ) leading to impairment of basic daily functions such as chewing and speaking. It is known as the most prevalent cause of nonodontogenic pain in the orofacial region, which 5–12% of the adult population experience [1]. Many factors have been identified to cause and exacerbate its symptoms including sleep quantity and quality, genetic, hormonal, anatomical, and psychosocial factors [2, 3].

Physical activity has been known to affect symptoms in various pain disorders. Exercise is significantly associated with lower perceived pain levels in fibromyalgia patients, while high-intensity exercise was reported to increase pain levels in fibromyalgia patients [4]. Low back pain is also known to be aggravated by higher activity levels [5]. The underlying mechanisms of such interactions are not fully understood. The increase in inflammatory mediators with high-intensity exercise may directly cause an increase in pain levels [6]. However, another previous study reported lower inflammatory biomarker levels including high sensitivity C-reactive protein (hsCRP) with moderate to vigorous physical activity [7], suggesting a complicated interaction between the two. Contradictory results can also be found in clinical reports regarding pain disorders, which involve regular physical activity [8, 9]. Such inconsistencies are largely due to the heterogeneity of the studies in defining physical activity levels and patient groups.

In spite of its profound impact on quality of life and high prevalence, no previous study has prospectively investigated the correlation between TMD and physical activity while considering well-known confounders such as psychological status and sleep quality in addition to hematological markers of systemic inflammation. Since the quantity and quality of sleep can significantly affect pain, it is also necessary to control its influences. Physical activity, sleep duration, and TMD pain are strongly interrelated as they affect one another through overlapping mechanisms.

## Objectives

Therefore, the main objectives of this “Physical Activity in TMD (PAT)” study are,To assess the long-term effect of objective physical activity level and sleep duration on clinical characteristics in well-defined TMD patient groups.To analyze the impact of physical activity on treatment response to conventional TMD management approaches by determining the cut-off value for physical activity that affects treatment prognosis.To define the causal relationship between abnormal physical activity levels and sleep durations on chronic, high-intensity TMD pain, its comorbidities, and systemic inflammatory marker levels.

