## Methods and design

### Participants, interventions, and outcomes

#### Study design

This is a longitudinal cohort study being conducted prospectively in Seoul National University Dental Hospital from May 2021. It was approved by the Institutional Review Board (IRB) of the same hospital (#CRI21007). The study is registered in Clinical Research Information Service, an online registration system for clinical researches (registration number KCT0007107). The system includes all items from the trial registration data set of the World Health Organization (version 1.3.1). Written informed consent is collected from all participants by YC. Further modifications to the study protocol that occur after IRB approval will be reported to the review board and relevant parties for additional permission. In case of any major modification of protocol version 1.0, the issue will be thoroughly discussed with the IRB. Whenever there is a change, a new protocol version will be assigned. All procedures complied with multiple ethical standards of the institutional research committee, the Helsinki declaration in 1964, and its later amendments or other equivalent ethical standards.

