#### Participants and eligibility criteria

Adult patients who are 18 years old or older with Korean nationality are included as participants. They visited the outpatient clinic of the Department of Oral Medicine of Seoul National University Dental Hospital with the chief complaint of pain and dysfunction of the temporomandibular joint and were diagnosed with TMD. The diagnoses were implemented according to the Diagnostic Criteria for TMD (DC/TMD) regardless of TMD subtype diagnosis or following treatment plan to allow further subgroup analysis [10]. Patients with previously diagnosed systemic musculoskeletal disorders including fibromyalgia, low back pain, rheumatoid arthritis, ankylosing spondylitis, gout, liver disease, kidney disease, an uncontrolled endocrine disorder, autoimmune disease, trauma within the last 6 months, treatment history for a psychiatric disorder that may affect the study, and primary sleep disorder diagnosis will be excluded.

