#### Interventions

All participants were treated with identical protocols after TMD diagnosis. The treatment protocols include conservative treatment such as consultation (explanation of the etiology and anatomy of the temporomandibular joint), management of contributing factors including tooth clenching, physical therapy (moist hot pack, ultrasound therapy, low-level laser therapy, medication, and transcutaneous electrical nerve stimulation), and occlusal splints with full coverage of the upper teeth with hard resin.

To promote the retention of participants, staff will contact those that are lost at the designated follow-up without rescheduling. Data from those that withdraw their consent to participate will not be included in the final analysis.

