##### Pain disability level evaluated with graded chronic pain scale (GCPS) of DC/TMD axis II

*Low disability TMD group* GCPS grade I and II (low disability-low intensity pain and low disability-high intensity pain, respectively).*High disability TMD group* GCPS grade III and IV (high disability-moderately limiting pain and high disability-severely limiting pain, respectively)

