#### Study outcomes

##### 3.1.6.1. Primary outcome measures: clinical outcomes listed below will be gathered at the participant’s first visit (baseline) and at 6- and 12-month post-treatment.

Amount of physical activity and sleep duration objectively measured using ActiGraph wGT3X-BT (ActiGraph, Florida, USA), a validated 3-axis accelerometer that includes ambient light sensors. Actigraphy is a method to monitor the cycles of rest and activity, which does not involve any invasive procedures. The movements of the accelerometer and light exposure can be continually recorded with a watch-like device worn on the wrist to objectively determine the amount of physical activity and sleep duration of a participant. Despite its limitations in measuring and staging sleep, actigraphy data provides real-life information on both the objective amount of physical activity and sleep by allowing the participant to maintain normal routines in his or her natural environment. Physical activity is measured at baseline only. (Fig. 1)*Amount of comfortable mouth opening* [12] the participant will be asked to open his or her mouth as wide as possible while remaining pain-free. If the participant is already experiencing pain, open as wide as possible without increasing current pain. Interincisal distance between the maxillary and mandibular reference teeth will be measured.*Amount of maximum mouth opening* [12] the participant will be asked to open as wide as possible, even if it is painful. Interincisal distance between the maxillary and mandibular reference teeth will be measured.*Muscle tenderness on palpation* [12] 12 masticatory muscle areas will be palpated on both sides including posterior, middle, and inferior temporalis muscle area and origin, body, and insertion of the masseter muscle with 1 kg of pressure.*Joint capsule tenderness on palpation* [12] 6 areas of TMJ will be palpated on both sides including the posterior, superior, and lateral parts of the capsule with 0.5 kg of pressure in a passive state. When palpation elicits subjective pain, the response will be recorded as positive. Joint noises are verified through palpation.*Subjective pain intensity* participant reported pain intensity based on a 0–10 numeric rating scale (NRS).

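### Objective 3 promises a causal relationship that an observational cohort, with activity measured once in patients already in pain, cannot establish

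*Protocol article*

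**What the plan says.** All references are to the protocol article.

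- **Objectives.** The third main objective is "To define the causal relationship between abnormal physical activity levels and sleep durations on chronic, high-intensity TMD pain", and it extends to comorbidities and systemic inflammatory markers.
- **Study design.** "This is a longitudinal cohort study being conducted prospectively".
- **Participants and eligibility criteria.** Patients attended the clinic "with the chief complaint of pain and dysfunction of the temporomandibular joint and were diagnosed with TMD".
- **Interventions.** "All participants were treated with identical protocols after TMD diagnosis". Activity is neither assigned nor changed by the study.
- **Primary outcome measures (3.1.6.1).** The heading says that the measures "will be gathered at the participant’s first visit (baseline) and at 6- and 12-month post-treatment". The item on actigraphy then says: "Physical activity is measured at baseline only". Whether the sleep part of the recording is repeated is not clear.
- **Background.** Activity, sleep duration and TMD pain are described as interrelated because "they affect one another through overlapping mechanisms".
- **Patient grouping.** Low disability is GCPS grade I–II and high disability is grade III–IV. No assessment time is given for the GCPS.
- **Statistical analysis.** Logistic regression looks for factors associated with a worse long-term prognosis. Pre-treatment TMD indices, psychosocial scores, sleep quality and blood indices enter with the actigraphy variables. Covariates are then removed one at a time, highest p-value first.
- **Abstract (Discussion paragraph) and the end of the Discussion.** The results are expected to lead to cause-related, personalised care and to support a guideline on physical activity.

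**The concern.** A causal objective needs a design or an analysis that can separate the direction of interest from its reverse. The protocol states the reverse path itself and names nothing that would separate the two. Activity is recorded once, after the disease has begun, so there is no pre-onset activity and no change in activity to set against later change in pain.

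The document also uses activity in both roles. The sample size section treats activity minutes as the outcome that differs between groups, while the regression treats actigraphy as a predictor of prognosis.

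What is at stake is what the study may conclude. An association produced wholly or partly by pain limiting activity could be reported as an effect of activity and carried into a guideline.

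**Working it through.** **Step 1. Baseline comparison.** Let S be pain severity and A be activity, both observed once at the same visit. A model in which A lowers S and a model in which S lowers A can give exactly the same joint distribution of (A, S). No sample size tells them apart. This applies to any comparison of baseline activity between GCPS groups assessed at baseline, and it needs no numerical assumption.

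**Step 2. Follow-up outcomes.** Here A precedes the outcome Y, so Y cannot have caused A. What remains is confounding by earlier severity: S may influence both A and Y. The planned adjustment removes this only as far as the covariates that stay in the model capture S. The Statistical analysis section protects them weakly. If the stated limit is read in the sense that fits removal from the highest p-value down, a covariate above 0.300 goes whatever it does to the odds ratio. The 10% change rule applies only between 0.250 and 0.300.

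**Step 3. Size of the residual bias (illustration).** The only input from the document is the sample size: 214 planned with 20% dropout gives 214 × 0.80 = 171.2, so n = 171. Everything else is assumed:
- there is no effect of A on Y;
- corr(S, A) = a = −0.3 (range −0.2 to −0.4);
- corr(S, Y) = b = 0.5;
- k baseline indices each measure S with reliability ρ and independent errors;
- the model is linear, with no elimination step.

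The k indices together have reliability R = kρ / [1 + (k − 1)ρ]. The partial correlation of A and Y given the indices is

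r = ab(1 − R) / √[(1 − a²R)(1 − b²R)].

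The two-sided 5% test rejects with probability of about Φ(−1.96 + |r|√(n − k − 3)) + Φ(−1.96 − |r|√(n − k − 3)).

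Worked case, one score with ρ = 0.5 (R = 0.5):
- r = −0.075 / √(0.955 × 0.875) = −0.082
- |r|√167 = 1.06
- Φ(−0.90) + Φ(−3.02) = 0.184 + 0.001 = 0.185

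Simulated rejection rates (10,000 replicates per cell) agree with the formula:

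| Adjustment | R | r at a = −0.3 | a = −0.2 | a = −0.3 | a = −0.4 |
|---|---|---|---|---|---|
| none | 0 | −0.150 | 26% | 50% | 75% |
| one score, ρ = 0.5 | 0.50 | −0.082 | 11% | 19% | 31% |
| one score, ρ = 0.7 | 0.70 | −0.051 | 7% | 10% | 15% |
| five indices, ρ = 0.3 | 0.68 | −0.054 | 7% | 11% | 16% |
| three indices, ρ = 0.5 | 0.75 | −0.043 | 7% | 9% | 12% |
| five indices, ρ = 0.5 | 0.83 | −0.029 | 5% | 7% | 8% |
| three indices, ρ = 0.3 | 0.56 | −0.073 | 10% | 15% | 24% |
| three indices, ρ = 0.7 | 0.88 | −0.022 | 5% | 6% | 6% |
| S itself | 1 | 0 | 5% | 5% | 5% |

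The last row shows that the excess comes from imperfect adjustment and not from the test. A logistic version with a dichotomised outcome, one score of reliability 0.7 and a severity–outcome correlation of √0.5 ≈ 0.71 gave 11% at a = −0.3. The one-score and several-index rows bracket roughly what elimination might leave in the model. They do not model the elimination itself.

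**The case against.** The strongest reply is that the analysis is already more modest than the objective. The regression speaks of factors associated with prognosis, exposure precedes outcome at 6 and 12 months, and pre-treatment symptom indices are candidate covariates alongside psychosocial, sleep and blood measures. The primary outcomes list five clinical indices, and adjusting for several of them brings the false-positive rate close to nominal in many settings. This stands for follow-up outcomes, and it is why the point is limited there to residual confounding. It does not help a baseline comparison, and it does not supply the causal identification that Objective 3 promises.

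Several stronger readings are tempting and are not supported:
- **That the whole GCPS, comorbidity and blood-marker comparison is cross-sectional.** The text does not date these assessments and the flowchart is not shown. The argument holds for whatever is compared at baseline.
- **That the study has a false-positive rate near 50%.** That figure belongs to an unadjusted test, which is not the planned prognostic model.
- **That a spurious protective effect of activity should be expected.** The document gives neither the sign nor the size of the pain–activity correlation, and the Background reports conflicting directions in other pain disorders.
- **That the single-measurement argument covers sleep equally.** The baseline-only statement names physical activity.
- **That a causal statement will be published.** That is conjecture. The text shows only that one is set as an objective.

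The point is also not one to leave to a separate analysis plan, which cannot add activity measurements that the protocol says are not taken.

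**Conclusion.** The point holds as a mismatch between objective and design. On the text alone, an observational cohort of patients already in pain, with one activity measurement and an acknowledged two-way relation, cannot define a causal relationship.

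For baseline comparisons the limitation is complete. For 6- and 12-month outcomes it is partial. Under the assumed values (no true effect, severity–activity −0.3, severity–outcome 0.5, n = 171) the false-positive rate is about 10–20% with one pain score of reliability 0.5–0.7. It is about 7–11% with three indices of reliability 0.5 or five of 0.3–0.5. Three weak indices (0.3) would give about 15% and three good ones (0.7) about 6%. These rates rest on correlations and reliabilities that the document does not give. They show that the residual bias can matter, not how large it will be in this study. The conclusion does not depend on them.

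**What to change.** 1. **Objective 3.** Remove the causal wording. State it as the association of baseline activity and sleep duration with pain, comorbidity and inflammatory markers at baseline, labelled cross-sectional, and with their later course where follow-up values are collected.
2. **Timing.** State when the GCPS, questionnaires and blood markers are taken, and whether sleep actigraphy is repeated.
3. **Statistical analysis.** In the prognostic model, keep the baseline value of the same outcome and baseline GCPS grade throughout, exempt from p-value elimination. Base any statement about prognosis on follow-up outcomes only.
4. **Abstract and Discussion.** Limit the cause-related and guideline statements to hypothesis generation.

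This is a change of wording and of model specification. It uses baseline clinical measures already in the plan, needs no new patients, and takes a few degrees of freedom in the model. The real cost is a weaker headline claim.

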## Methods and design

### Participants, interventions, and outcomes

#### Study design

This is a longitudinal cohort study being conducted prospectively in Seoul National University Dental Hospital from May 2021. It was approved by the Institutional Review Board (IRB) of the same hospital (#CRI21007). The study is registered in Clinical Research Information Service, an online registration system for clinical researches (registration number KCT0007107). The system includes all items from the trial registration data set of the World Health Organization (version 1.3.1). Written informed consent is collected from all participants by YC. Further modifications to the study protocol that occur after IRB approval will be reported to the review board and relevant parties for additional permission. In case of any major modification of protocol version 1.0, the issue will be thoroughly discussed with the IRB. Whenever there is a change, a new protocol version will be assigned. All procedures complied with multiple ethical standards of the institutional research committee, the Helsinki declaration in 1964, and its later amendments or other equivalent ethical standards.

#### Participants and eligibility criteria

Adult patients who are 18 years old or older with Korean nationality are included as participants. They visited the outpatient clinic of the Department of Oral Medicine of Seoul National University Dental Hospital with the chief complaint of pain and dysfunction of the temporomandibular joint and were diagnosed with TMD. The diagnoses were implemented according to the Diagnostic Criteria for TMD (DC/TMD) regardless of TMD subtype diagnosis or following treatment plan to allow further subgroup analysis [10]. Patients with previously diagnosed systemic musculoskeletal disorders including fibromyalgia, low back pain, rheumatoid arthritis, ankylosing spondylitis, gout, liver disease, kidney disease, an uncontrolled endocrine disorder, autoimmune disease, trauma within the last 6 months, treatment history for a psychiatric disorder that may affect the study, and primary sleep disorder diagnosis will be excluded.

#### Interventions

All participants were treated with identical protocols after TMD diagnosis. The treatment protocols include conservative treatment such as consultation (explanation of the etiology and anatomy of the temporomandibular joint), management of contributing factors including tooth clenching, physical therapy (moist hot pack, ultrasound therapy, low-level laser therapy, medication, and transcutaneous electrical nerve stimulation), and occlusal splints with full coverage of the upper teeth with hard resin.

To promote the retention of participants, staff will contact those that are lost at the designated follow-up without rescheduling. Data from those that withdraw their consent to participate will not be included in the final analysis.

#### Recruitment of cases

Data will be gathered sequentially from all participants visiting the participating hospital for TMD and provide written informed consent from July 2021. Recruitment will proceed for 12 months and may be prolonged when the number of cases is insufficient. The final sample size is estimated to be approximately 200 participants based on a previous study on rheumatoid arthritis using statistical sample size estimation methods (α = 0.05, β = 0.10) [11].

#### Patient grouping

TMD patients diagnosed with DC/TMD are grouped according to two different criteria.

##### Pain disability level evaluated with graded chronic pain scale (GCPS) of DC/TMD axis II

*Low disability TMD group* GCPS grade I and II (low disability-low intensity pain and low disability-high intensity pain, respectively).*High disability TMD group* GCPS grade III and IV (high disability-moderately limiting pain and high disability-severely limiting pain, respectively)

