##### Amount of time counted as moderate to vigorous physical activity (MVPA)

*Inactive* less than 150 min per week engaging in moderate-intensity physical activity and less than 75 min per week engaging in vigorous-intensity physical activity*Active* 150 min or more per week engaging in moderate-intensity physical activity or 75 min or more per week engaging in vigorous-intensity physical activity

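### The Active/Inactive rule tests moderate and vigorous minutes separately, so the groups are not ordered by MVPA time; secondarily, the disability split does not isolate the high-intensity pain of Objective 3

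*Protocol article*

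**What the plan says.** The Patient grouping section of the protocol article sets two groupings.

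**Activity.** The subsection heading names the amount of MVPA time as the basis. A patient is Active with "150 min or more per week engaging in moderate-intensity physical activity or 75 min or more per week engaging in vigorous-intensity physical activity". Inactive requires less than 150 moderate minutes and less than 75 vigorous minutes. The rule does not mention the two added together. Under Study outcomes, physical activity is measured by accelerometer at baseline only, so each patient is classified once.

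**Pain.** The heading is "Pain disability level evaluated with graded chronic pain scale (GCPS) of DC/TMD axis II". The low-disability group is "GCPS grade I and II (low disability-low intensity pain and low disability-high intensity pain, respectively". The high-disability group is "GCPS grade III and IV (high disability-moderately limiting pain and high disability-severely limiting pain, respectively".

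Two other places describe the pain side differently. The abstract (Methods and design) states: "The collected data will be analyzed according to TMD pain severity and physical activity level". Objective 3 is directed at "chronic, high-intensity TMD pain, its comorbidities, and systemic inflammatory marker levels".

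**The concern.** Activity is the exposure that the study is named for. If the groups are meant to rank patients by MVPA time, a patient with more of it should not be called Inactive while one with less is called Active. A rule that looks at each intensity alone allows this for anyone who accumulates time in both but passes neither cut-off. The Active and Inactive labels would then not mean what the heading says, and any comparison between the groups would be hard to interpret.

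The pain issue is smaller. Objective 3 and the abstract speak of intensity and severity, but the only pain grouping defined is by disability. If that split were taken as the test of Objective 3, patients whom the article itself describes as having high-intensity pain would sit in the comparison group.

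**Working it through.** The article gives no figure of its own on this point to reproduce. Its sample size of 214 does not depend on it. The check applies the stated rule to whole-minute values.

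**Inputs.** The cut-offs, 150 moderate and 75 vigorous min/week, come from the MVPA subsection of Patient grouping. Let M and V be weekly moderate and vigorous minutes.

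- Active: M >= 150 or V >= 75.
- Inactive: M < 150 and V < 75. This is the exact complement, so nobody is left unclassified.
- Total MVPA: T = M + V.
- Moderate-equivalent time: E = M + 2V. The weight 150/75 = 2 is an inference from the two cut-offs; the article does not state it.

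| M | V | T | E | Group |
|---|---|---|---|---|
| 149 | 74 | 223 | 297 | Inactive |
| 140 | 70 | 210 | 280 | Inactive |
| 120 | 60 | 180 | 240 | Inactive |
| 100 | 50 | 150 | 200 | Inactive |
| 149 | 0 | 149 | 149 | Inactive |
| 150 | 0 | 150 | 150 | Active |
| 0 | 75 | 75 | 150 | Active |

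**Ordering on total minutes.** Inactive extends up to 149 + 74 = 223; Active begins at 0 + 75 = 75. Any total from 75 to 223 can fall in either group. This needs no weighting.

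**Ordering on weighted minutes.** Inactive extends up to 149 + 2 x 74 = 297, which is 297/150 = 1.98 times the moderate cut-off; Active begins at 150. The groups overlap on this scale too.

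**Who is affected.** An Inactive patient has V of at most 74, so reaching T = 150 needs M of at least 150 - 74 = 76. M is at most 149, so it also needs V of at least 1. The patients affected have mixed profiles below both cut-offs. Patients with only one kind of activity are ordered correctly on E.

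**Extent of the rule's overlap.** The Inactive region holds 150 x 75 = 11,250 whole-minute combinations. T >= 150 holds in 2,775 of them (24.7%) and E >= 150 in 5,550 (49.3%). These are shares of combinations, not of patients, whose distribution is not given.

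**Effect of a combined rule, E >= 150.** If M >= 150 or V >= 75, then E >= 150, so no Active patient changes group. Only Inactive patients can move. Afterwards Inactive stops at E = 149 and Active starts at E = 150, so the groups are ordered on E.

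**Pain passages side by side.** The grouping's heading, its two labels and its content all concern disability, and grade II is described there as low disability, so the rule agrees with itself. Grade II is also described as high intensity, while grades III and IV are described by limitation, with no intensity stated. The split therefore does not separate high-intensity from low-intensity pain, which is what Objective 3 and the abstract's wording call for.

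**The case against.** **The article sets no combined threshold.** This stands. Separate cut-offs are a coherent rule in themselves, and the 2:1 weight is inferred, so one cannot say that the 210-minute patient exceeds a limit the article sets. The misordering on plain minutes remains, because the heading names MVPA time and the rule does not rank patients by it.

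**The moderate cut-off might be meant to count all time at moderate intensity or above.** Then 140 + 70 would be Active. The text does not say so; if that is the intention, it needs stating.

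**Only mixed profiles are affected, perhaps few.** This also stands as far as it goes: the number cannot be known from the document.

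**The two-way split is not the only use of the activity data.** The Statistical analysis section enters continuous actigraphy measures such as energy consumption, metabolic equivalents and step count, and explores thresholds by ROC curves. Objective 2 seeks a cut-off from the data. This limits the consequences and is why the point does not ask for continuous MVPA to become the main exposure. Group comparisons are still planned, and the abstract says the data will be analysed by activity level.

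**The disability grouping is sound.** This stands in full. A reader might infer that placing grade II in the low group contradicts the grouping's own construct. It does not: the construct is disability, and pain disability is a declared secondary outcome in the abstract. A reader might also infer that Objective 3 cannot be answered. That is not supported either. Pain intensity on a 0-10 scale is a primary outcome at baseline, 6 and 12 months, logistic regression on prognosis in terms of pain and function is planned, and nothing ties Objective 3 to the disability split alone.

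**Conclusion.** The activity point holds. As written, the Inactive group can include patients with up to 223 min/week of MVPA while the Active group admits patients with 75, so the groups are not ordered by the quantity in their heading. The result on total minutes rests only on the stated cut-offs, read as applying to moderate and vigorous time separately. The figure of 297 weighted minutes also assumes the 2:1 weight.

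A reader might infer that the comparison is pulled towards no difference. The document does not establish this. The distribution of mixed profiles is not reported, and the Background cites both lower pain with exercise and higher pain with high-intensity exercise, so the direction is open.

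The pain point holds only as a mismatch between sections: the disability split is valid, but it is not a grouping by pain intensity or severity. A reader might want to put a percentage on how far an intensity effect would be diluted. That would need the share of grade II in the low group and the share of high-intensity pain in grades III and IV. The article gives neither, so no figure is offered.

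**What to change.** 1. Define Active by one combined measure, for example moderate + 2 x vigorous >= 150 min/week, and Inactive otherwise. State that the 2:1 weight is taken from the article's own 150 and 75 cut-offs, and word the heading as weighted MVPA time. If plain total minutes are preferred, say so and give the cut-off.
2. Keep the present split as a sensitivity analysis and report how many patients change group.
3. For Objective 3, use the 0-10 numeric rating scale as the measure of pain intensity. Keep GCPS I-II versus III-IV as the disability analysis that it is.
4. Reconcile the wording of the abstract (pain severity), Objective 3 (high-intensity pain) and the GCPS grouping (disability).

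The cost is re-derivation from baseline actigraphy, since the present rule already needs moderate and vigorous minutes separately, plus a few sentences of text. No new measurement is required. The article describes data collection as in process and analysis as ongoing, so the change should be dated and documented as a protocol modification before the groups are compared.
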